### 5. Trial methods

On arrival to hospital, patients will be assented for IMR during their primary PCI. Following thromboaspiration, restoration of flow, and deployment of intracoronary stent. IMR will be performed following completion of standard PPCI care. All acute coronary syndrome medical treatment will be unaffected. Consent for continued inclusion in the study will be performed at 24 hours. At day 2-4 following myocardial infarction, baseline CMR will be undertaken. This will be repeated at 3 months. Blood samples for biomarkers will be taken at the time of angioplasty, at 24 hours and at the 3 months CMR follow up visit.

#### 5.1 Research procedures

In addition to standard care for STEMI, patients will have IMR measured following stent deployment in the catheter lab. They will also have 2 CMR scans; 1 at baseline (day 2-4) and 1 at 3 months follow-up. Blood samples for biomarkers will be taken at baseline, 24 hours and 3 months.

#### 5.2 Duration of treatment period

Patients will be included in the study until their 3 month follow up CMR is completed.

### **5.3 Definition of end of trial**

End of trial will be confirmed when the final patient has completed the 3 month follow up CMR.

### **5.4 Data collection**

Data collection will include the following elements:

- (a) A log of STEMI patients who are approached for the study (including the date when they are given the Patient Information Leaflet (PIL)).
- (b) Patients approached and assessed against the eligibility criteria.
- (c) Assent, consent and baseline information (history, ECG, troponin and angiogram results) collected.
- (d) CMR scan data
- (e) IMR data
- (f) Biomarker results

| Exam                      | Time scale    |             |       |       |         |
|---------------------------|---------------|-------------|-------|-------|---------|
|                           | Pre-treatment | During PPCI | Day 1 | Day 2 | Month 3 |
| MRI                       |               |             |       | X     | X       |
| Assent                    | X             |             |       |       |         |
| Informed consent          |               |             | X     |       |         |
| IMR                       |               | X           |       |       |         |
| Blood test for biomarkers |               | X           | X     |       | X       |

**Table 1 Data collection**

### 5.5 Planned recruitment rate

We plan to recruit 50 consecutive patients who meet the inclusion/ exclusion criteria. BHI admits > 600 STEMI patients a year. We expect recruitment to last 3 months (estimated 11 STEMI patients a week, we estimate one third of these will be eligible for recruitment).

### 5.6 Participant recruitment

Patients presenting with STEMI and meeting inclusion/ exclusion criteria will be invited to participate. Potential trial participants will be identified in the catheter lab as they present with STEMI through the PPCI service. A verbal explanation of the planned trial will be given and verbal assent to be included taken. This is in accordance with previous and current studies running in the department (Comfortable, Erupt, Pinpoint). Following PPCI, the patients will be transferred to the coronary care unit. All participants will be given a PIL (approved by the local Research Ethics Committee (REC)) describing the study. The patient will have time to read the PIL and to discuss their continuation in the study with others outside the research team (e.g. relatives or friends) if they wish. Most patients will have at least 6 hours to consider whether to participate. Despite the short notice, it is important to include these patients as the changes on CMR following STEMI are time critical and waiting longer would not be possible.

After admission to the coronary care unit following their STEMI, patients will be seen by a member of the local research team (study clinician/research nurse/trial co-ordinator) who will answer any questions, confirm the patient's eligibility and take written informed consent if the patient decides to continue in the study. Details of all patients approached for the trial and reason(s) for non-participation (e.g. reason for being ineligible or patient refusal) will be documented.

### 5.7 Discontinuation/withdrawal of participants

Participants/ clinicians may withdraw from the trial by contacting a member of the research team. If IMR data and CMR scans have been completed, the data will still be collected and included in the data analysis.

If a participant wishes to withdraw, we will continue to analyse any data already collected, unless the participant expresses a wish for their samples and any associated data to be destroyed.

## **5.8 Frequency and duration of follow up**

In addition to standard PPCI out patient clinic follow up, patients will be followed up at 3 months with CMR and biomarker blood testing.

## **5.9 Likely rate of loss to follow-up**

Until discharge from hospital, the only losses to follow-up will be due to death or a participant withdrawing; these losses are expected to be very few. We expect loss to 3 month follow-up to be minimal.

## **5.10 Expenses**

Reimbursement of travel expenses for the 3 month follow up CMR visit will be offered.

## **5.11 Measures taken to avoid bias**

This is a non randomised trial enrolling consecutive consenting eligible STEMI patients.

The IMR analysis will be performed by observers blinded to the CMR data.

The CMR analysis will be performed by observers blinded to the IMR data.

Biochemical markers will be measured by an independent laboratory technician, without knowledge of IMR or CMR data.

# **6. Statistical analyses**

## **6.1 Plan of analysis**

Continuous data will be summarised using means and standard deviations (or median and interquartile range if the distribution is skewed). Category variables will be reported at a frequency and percentage. The association between the primary outcome, MVO at 2-4 days and IMR will be quantified using multiple linear regression, assuming the measures will be transformed (e.g. to a logarithmic scale) as necessary to induce normality. The analysis will be adjusted for three covariates – age, gender and time since MI. The relationship between the outcome and each predictor will be explored graphically and the model will be extended to include non-linear functions if non-linear relationships are indicated.

Secondary outcomes will also be analysed using multiple linear regression (continuous measures) or logistic regression (binary measures). Continuous outcomes measured at both 2-4 days and at 3 months will be modelled using a mixed regression model, which will account for the correlation between repeated measurements on the same individual. If a baseline value is also available this will be measured jointly with the subsequent measures.

Associations will be quantified and reported with 95% confidence intervals.

## **6.2 Frequency of analyses**

The primary analysis will take place when follow-up is complete for all recruited participants. No formal interim analysis is planned.

## **7. Trial management**

The trial will be managed by the Trial Management Group (TMG). The TMG will prepare all the trial documentation and data collection forms, develop and maintain the study database, check data quality as the trial progresses, monitor recruitment and carry out trial analyses with advice from the Clinical Trials and Evaluation Unit (CTEU) Bristol.

### **7.1 Day-to-day management**

The trial will be managed by a Trial Management Group (TMG), which will meet approximately monthly. The TMG will be chaired by a Chief Investigator and will include all members of the named research team (see *Chief Investigators & Research Team Contact Details*).

An appropriately qualified person by training will be responsible for identifying potential trial participants, seeking informed participant consent, collecting trial data and ensuring the trial protocol is adhered to.

### **7.2 Monitoring of sites**

#### **7.2.1 Initiation visit**

Before the study commences training session(s) will be organised by TMG. These sessions will ensure that personnel involved fully understand the protocol, CRFs and the practical procedures for the study.

#### **7.2.2 Site monitoring**

The study will be monitored in line with the sponsors monitoring policy.

### **7.3 Trial Steering Committee and Data Monitoring and Safety Committee**

The Cardiovascular Research Board (CRB) has been established to oversee cardiovascular projects being carried out by the partnership between Hospitals Bristol NHS Foundation Trust (UH Bristol) and the University of Bristol (primarily, component projects of National Institute for Health Research (NIHR) Applied Programme Grants, the NIHR Cardiovascular Biomedical Research Unit (BRU)). The CRB is made up of representatives of UH Bristol and the University of Bristol. The Board will act as the Trial Steering Committee for this and other single centre trials in these NIHR programmes. The Board is chaired by the Director of the BRU, [name].

## **8. Safety reporting**

Serious and other adverse events will be recorded and reported in accordance with the International Conference for Harmonisation of Good Clinical Practice (ICH GCP) guidelines and the Sponsor's Research Related Adverse Event Reporting Policy (see Figure 2). The UH Bristol perform this role on behalf of the University of Bristol.

CMR is a safe imaging technique with no ionising radiation. There is a small risk due to contrast administration. These side effects are not unexpected. The research team will only notify fatal and 'unexpected' non-fatal SAEs to the Trial Sponsor. Unexpected events are those not listed in the trial protocol or on the CRFs. The sponsor will inform the TMG if the event needs to be reported to the REC (usually only events that are both related to the intervention and unexpected e.g. SUSARs see Figure 2).

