### 4.3 Trial population

#### • Study population:

Male and female patients (>18 years old) presenting with a suspected STEMI (ST-elevation on electrocardiogram) within 12 hours of chest pain. No coronary collaterals and TIMI flow <1.

• **Planned interventions:**

**STEMI patients intervention as part of clinical care:** On arrival to hospital, emergency patients with STEMI will be taken directly to the cardiac catheterisation for primary PCI. This is time critical with national targets of door to balloon time of 60 mins. Standard primary PCI treatment includes thromboaspiration and restoration of flow with stent deployment.

**STEMI patients additional measurement as part of research study:** Following completion of standard treatment of the heart attack, the IMR measurement will be performed; a pressure thermistor wire will be passed through the catheter already in situ for the PPCI. To achieve maximal hyperaemia for this measurement, an infusion of adenosine will be administered via a peripheral cannula. Verbal assent for inclusion in the study and this measurement will be performed on arrival in the catheter lab following the explanation of the PPCI. This is in accordance with previous and current studies in the department (Comfortable, Pinpoint, Erupt).

All acute coronary syndrome medical treatment will be unaffected. Consent for continued inclusion in the study will be performed at 24 hours.

At day 2-4 following myocardial infarction, baseline CMR will be undertaken. This will be repeated at 3 months. Blood samples for biomarkers will be taken at the time of angioplasty, at 24 hours and at the 3 months CMR follow up visit.

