| Gastrointestinal disorders                           |        | Nausea                                                                             | Vomiting               |                                                                                     |
| Skin and subcutaneous tissue disorders               |        |                                                                                    | Urticaria, Rash        | Face oedema, Hyperhidrosis, Pruritus, Erythema                                      |
| General disorders and administration site conditions |        | Injection site pain, Injection site reaction                                       |                        | Nephrogenic Systemic Fibrosis (NSF), Feeling hot, Malaise                           |

Perioperative MI, including:

Raised Troponin T or Troponin I

Cardiac arrest, requiring:

- Resuscitation involving ventricular defibrillation/DC shock
- Chest reopening
- External/internal cardiac massage

Haemodynamic support, including use of:

- Any inotropes
- IABP

- Pulmonary artery catheter
- Vasodilator
- Low cardiac output, requiring management with a Swan-Ganz catheter, an intra-aortic balloon pump, or left ventricular assist device

Arrhythmias, including:

- Supraventricular tachycardia or atrial fibrillation requiring treatment
- VF/VT requiring intervention
- Pacing

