## 8.2 Period for recording serious adverse events

Data on adverse events will be collected from the time of assent to the end of the second scan.

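### Sponsor notification depends on event name alone, so a non-fatal arrest or VT during the research-only IMR measurement counts as expected and is recorded but not notified

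*Protocol*

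**What the plan says.** Protocol section 8 sets the route from site to sponsor, and defines its key term in the next sentence: the team notifies only fatal and unexpected "non-fatal SAEs to the Trial Sponsor. Unexpected events are those not listed in the trial protocol or on the CRFs". After that, the sponsor tells the trial management group whether an event must go to the ethics committee, which is usually the case only for events that are both related and unexpected. The section opens by invoking ICH GCP, the sponsor's adverse event reporting policy and Figure 2.

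Section 8.1 is the list. It contains failure to complete the scan because of claustrophobia, a table of contrast reactions, and then a block with no heading of its own. That block begins "Perioperative MI, including" and goes on to cardiac arrest (with "Chest reopening" and internal massage among the responses), haemodynamic support, and arrhythmias including VF/VT and pacing.

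Section 4.3 describes the IMR measurement under the label "STEMI patients additional measurement as part of research study". It follows completion of standard PPCI and uses a pressure thermistor wire. For the hyperaemia it needs, "an infusion of adenosine will be administered via a peripheral cannula".

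**The concern.** The infusion and the wire are added to care for the study's sake, so serious events during them are ones the sponsor would want to hear about promptly. Section 4.3.2 excludes patients with known allergy to adenosine, so the protocol treats the drug as a possible hazard. Yet the discussion of risk in section 8 covers only CMR and contrast, and section 9.2 calls the added risk of IMR negligible without itemising it.

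The notification rule asks neither what caused an event nor whether a research procedure may have contributed. If a serious event during IMR has a name that appears anywhere on the list, the site has no stated duty to notify it unless it is fatal. The sponsor would then not be alerted, and the question of relatedness would not be put to it. Section 6.2 plans no formal interim analysis, and section 7.3 describes a board acting as steering committee but no separate safety committee. Sponsor notification is therefore the main prompt safety channel that the protocol describes.

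**Working it through.** No arithmetic applies, and the plan states no figure to reproduce. The check applies the rule in section 8 to the list in section 8.1 for an event during the procedure in section 4.3.

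1. **Is the procedure covered by safety recording?** Yes. Section 8.2 starts collection at assent. Table 1 in section 5.4 places assent before treatment and IMR during PPCI.
2. **Is the event serious?** Yes. The glossary's SAE definition includes life-threatening events, which a non-fatal cardiac arrest meets. VF/VT that has to be treated would ordinarily meet it too.
3. **Is the event listed, and is a cause attached?**

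| Event during IMR | Where listed in section 8.1 | Cause attached? | Result under section 8 |
|---|---|---|---|
| Non-fatal cardiac arrest | Contrast table, and again in the block after it | None in the block | Expected, not notified |
| VF/VT needing intervention | Block after the table | None | Expected, not notified |
| Need for pacing | Block after the table | None | Expected, not notified |
| Inotropes or balloon pump | Block after the table | None | Expected, not notified |
| Any fatal event | Not relevant | Not relevant | Notified |
| Non-fatal SAE not on the list or CRFs | Not listed | Not relevant | Notified |

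4. **Could the block be confined to contrast reactions because it follows that table?** Not sensibly. Raised troponin, chest reopening and intra-aortic balloon support are not contrast reactions. The definition in section 8 also refers to being listed in the protocol at all, not under a particular heading.
5. **Where does relatedness enter?** Only when the sponsor decides on referral to the ethics committee. An event that section 8 keeps from the sponsor does not reach that decision.
6. **Does the block fit this study?** In part. Arrest, arrhythmia and haemodynamic support are plausible background events in STEMI patients undergoing PPCI. Perioperative MI, chest reopening and internal massage match none of PPCI, IMR or CMR.

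**The case against.** The strongest reply is that arrest, arrhythmia and haemodynamic support are part of the background course of STEMI, and that treating them as expected is a reasonable way to avoid flooding the sponsor. That stands for events unrelated to a research procedure. It does not explain why a possibly related event should be treated in the same way.

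A second reply is that section 8 defers to ICH GCP, the sponsor's policy and Figure 2, any of which might require a relatedness check before notification. The glossary also ties a SUSAR to a suspected product and its product information, so the protocol is not wholly blind to cause. This limits certainty about practice. However, section 8 uses the SUSAR idea only at the ethics-committee step, and its notification sentence contains no relatedness condition. If the policy does contain one, the two texts conflict and need reconciling.

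A reader might infer several stronger points that the documents do not support:

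- *The missing adenosine or pressure-wire entry causes the gap.* The opposite is true. Under this rule an unlisted event is unexpected and is notified, so the omission by itself increases notification. The surgical lines do not filter IMR events either; they are simply out of place.
- *Bronchospasm or circulatory collapse during the infusion would also be filtered out.* Both appear only under the contrast heading, and IMR precedes the first study scan, so a site could fairly treat them as unlisted.
- *The sponsor could not examine IMR risk, or events are lost.* Collection runs "from the time of assent to the end of the second scan", and sections 10.3 and 10.4 give the sponsor access to source data and study documents. What is lost is prompt individual notification.
- *A bound on the event rate from 50 patients measures the harm.* Such a bound follows from the sample size and would be the same under any notification rule.
- *The recording window is too short for late contrast reactions.* The protocol gives no onset times for the listed reactions, so this cannot be shown from it.

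**Conclusion.** The point holds as a gap in wording. Section 8 decides sponsor notification by event name, and section 8.1 lists cardiac arrest, VF/VT, pacing and haemodynamic support without a cause. A non-fatal event of these kinds during the research-only IMR measurement is therefore recorded but not notified, and its possible relatedness is not put to the sponsor.

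The gap has no numerical size. It affects every participant who has IMR (50 planned), is limited to non-fatal SAEs named on the list, and concerns prompt notification rather than data capture. The conclusion rests on a literal reading of section 8 and assumes that no overriding relatedness step sits in Figure 2, the CRFs or the sponsor's policy, none of which could be seen. Even if one does, the wording of section 8 needs correcting, because it tells site staff that they will notify only fatal and unlisted events. It should be changed, since the correction is cheap and improves oversight of the procedure that the study adds.

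**What to change.** Make four changes, all in section 8:

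- State that any SAE judged possibly related to a research procedure (adenosine infusion, pressure wire, contrast CMR) is notified to the sponsor whether or not it is listed.
- Let the generic cardiac items in section 8.1 count as expected only when judged unrelated to a research procedure.
- Remove perioperative MI, chest reopening and internal massage from the list.
- Reconcile the revised wording with Figure 2, the CRFs and the sponsor's reporting policy, so that site staff have one rule.

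The cost is a protocol wording amendment, a relatedness judgement by the site for each SAE before it decides on notification, and a few extra notifications. Treatment, study procedures, sample size and analysis are unchanged.

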### **8.1 Expected adverse events**

The following adverse events are 'expected':

Inability to complete the scan due to claustrophobia

## Side effects due to contrast administration

|                                                      |        | Adverse reactions from clinical trial data (experience in more than 2900 patients) |                        | Additional adverse reactions from postmarketing spontaneous reporting               |
|------------------------------------------------------|--------|------------------------------------------------------------------------------------|------------------------|-------------------------------------------------------------------------------------|
| System Class                                         | Organ  | Uncommon                                                                           | Rare                   | Rare                                                                                |
| Immune disorders                                     | system |                                                                                    | Anaphylactoid reaction | Anaphylactoid shock                                                                 |
| Nervous disorders                                    | system | Headache, Dizziness, Paraesthesia, Dysgeusia                                       | Parosmia               | Loss of consciousness, Convulsion                                                   |
| Eye disorders                                        |        |                                                                                    |                        | Conjunctivitis, Eyelid oedema                                                       |
| Cardiac disorders                                    |        |                                                                                    |                        | Cardiac arrest, Tachycardia                                                         |
| Vascular disorders                                   |        | Vasodilation                                                                       | Hypotension            | Circulatory collapse, Flushing                                                      |
| Respiratory, thoracic and mediastinal disorders      | and    |                                                                                    | Dyspnoea               | Respiratory arrest, Bronchospasm, Cyanosis, Oropharyngeal swelling, Cough, Sneezing |
| Gastrointestinal disorders                           |        | Nausea                                                                             | Vomiting               |                                                                                     |
| Skin and subcutaneous tissue disorders               |        |                                                                                    | Urticaria, Rash        | Face oedema, Hyperhidrosis, Pruritus, Erythema                                      |
| General disorders and administration site conditions |        | Injection site pain, Injection site reaction                                       |                        | Nephrogenic Systemic Fibrosis (NSF), Feeling hot, Malaise                           |

Perioperative MI, including:

Raised Troponin T or Troponin I

Cardiac arrest, requiring:

- Resuscitation involving ventricular defibrillation/DC shock
- Chest reopening
- External/internal cardiac massage

Haemodynamic support, including use of:

- Any inotropes
- IABP

- Pulmonary artery catheter
- Vasodilator
- Low cardiac output, requiring management with a Swan-Ganz catheter, an intra-aortic balloon pump, or left ventricular assist device

Arrhythmias, including:

- Supraventricular tachycardia or atrial fibrillation requiring treatment
- VF/VT requiring intervention
- Pacing

